#### Secondary outcomes

Time to completion of testing from randomisation, time to diagnosis from
randomisation and time to treatment from randomisation for new pathway (intervention
group) versus usual care. For those diagnosed with moderate-to-severe OSA (as
detailed above for both the intervention and usual care groups) and OSAS, their
AcuPebble or GP notes will be reviewed 6 months after randomisation to
determine time to completion of testing, time to diagnosis, time to commencement of
treatment and type of treatment prescribed. For the usual care pathway, we will also
look at the individual components of the usual referral pathway, that is, time to
test from referral, time to diagnosis from referral, time to treatment from
referral. Date of referral is defined as date when the patient was referred.Detection of participants diagnosed with any OSA (mild, moderate, severe), defined
as an AHI reading of ≥5 to <15 (mild), ≥15 to
<30 (moderate) or ≥30 (severe) episodes per hour for new
(intervention) versus usual care pathway. This will be determined from the AcuPebble
report for those in the intervention group and the GP notes review for those in the
usual care group.Detection of participants diagnosed with OSAS, defined as those with OSA (mild,
moderate, severe (as above)) and with evidence of EDS (ESS score >11) for new
(intervention) versus usual care pathway. This will be determined from the AcuPebble
report for those in the intervention group and the GP notes review for those in the
usual care group.Health-related quality of life associated with new and current pathways. QALYs will
be calculated based on information collected from participants at baseline and
6 months using the EQ-5D-5L.Cost-effectiveness analysis comparing new and current pathways. All participants
will be sent follow-up questionnaires either by email or post (as detailed above);
these will include the EQ-5D-5L with VAS, CSRI and information about procedures
undertaken to diagnose or treat moderate-to-severe OSA since randomisation. Further
data on health service usage will be obtained from the participant notes review
undertaken at 6-month follow-up. This review will collect data on service usage
related to sleep issues in the 6 months prior to date of randomisation to
provide a baseline value and during the 6 months after randomisation to
provide follow-up data.Feasibility and acceptability of new sleep study testing to be tested against the

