### Sample size determination

The detection rate of new cases of moderate-to-severe OSA using usual care is estimated
at <5% per year. Given the previously observed rates of hypertension (39%), obesity
(34%) and diabetes mellitus (15%) in individuals with OSA, we would expect that the
targeted case finding intervention would yield a detection rate of 10% or more in the
high-risk groups. The study has been powered (90%) at 5% two-sided significance level to
detect a 5% difference in rate of new cases of moderate-to-severe OSA between intervention
and usual care. The study will require 606 participants in each arm. To allow for 15%
attrition and lost to follow-up, it is anticipated that 713 in each arm need to be
recruited.

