## Statistical methods

Feasibility outcomes will be assessed descriptively and reported to the data monitoring and
safety committee and trial steering committee.

The study results will be reported in accordance with the Consolidated Standards of
Reporting Trials 2010 reporting guidelines (www.consort-statement.org/downloads/consort-statements) and a statistical
analysis plan will be prepared before recruitment starts.

Baseline variables will be presented by randomised group descriptively. Trial results
presented as comparative summary statistics with 95% CIs. All tests will be done at a 5%
two-sided significance level.

The primary analysis will include all randomised participants, as defined by protocol
eligibility criteria, regardless of what intervention they actually received or compliance
of intervention. The primary analysis of the primary outcome (detection of
moderate-to-severe OSA) will be performed using a logistic generalised linear mixed effects
model, adjusting for minimisation factors (age, sex and ethnicity) as fixed effect and
general practices as random effect. A similar approach will be used for other secondary
binary outcomes. Time-to-event outcomes will be analysed using a Cox regression model with
similar adjustment as the primary analysis. Secondary analysis of time to starting treatment
will include the primary analysis population who were diagnosed with moderate-to-severe OSA
and individuals with evidence of EDS/OSAS. Participants not starting treatment will be
censored at last contact date.

Missing data will be reported and the missing data pattern will be explored. Additional
sensitivity analysis using imputation methods will be performed. Safety outcomes of the
intervention will be descriptive.

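### The Cox analysis of time to starting treatment is restricted to participants diagnosed after randomisation, so its hazard ratio is not a randomised comparison

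*Protocol article*

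**What the plan says.** All quotations are from the protocol article.

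- **Model.** Statistical methods: "Time-to-event outcomes will be analysed using a Cox regression model with" adjustment similar to the primary analysis. That sentence names no population.
- **Population for time to treatment.** The next sentence says this analysis "will include the primary analysis population who were diagnosed with moderate-to-severe OSA" and individuals with EDS/OSAS. Those who do not start treatment are censored at last contact.
- **Which times are obtained.** Secondary outcomes presents times to testing, diagnosis and treatment, all from randomisation, as a comparison of the two pathways. For those diagnosed with moderate-to-severe OSA and OSAS, the AcuPebble report or GP notes are used to "determine time to completion of testing, time to diagnosis, time to commencement of" treatment.
- **Notes review.** Follow-up collects usual-care times only for participants with a positive diagnosis. It does not review the GP notes of intervention participants who tested negative and need no further follow-up.
- **Expected effect on diagnosis.** Sample size determination puts usual care below 5% per year and expects that the "targeted case finding intervention would yield a detection rate of 10% or more in the" high-risk groups.

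**The concern.** The set analysed for time to treatment is defined by an event that follows randomisation and that the intervention is designed to change. Control members of the set presented with symptoms, were referred and were diagnosed within 6 months. Intervention members come from testing everyone allocated to the device, so they include people usual care would not have found. Membership through EDS/OSAS is also settled after randomisation. The Epworth scale sits on the sleep study platform in the intervention arm, OSAS comes from GP notes in usual care, and the scale is not among the listed baseline questionnaires.

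Randomisation does not balance these sets. Adjusting for age, sex, ethnicity and practice cannot restore comparability in symptoms, severity or readiness to accept treatment. A hazard ratio from this model could be reported as the effect of the new pathway on speed of treatment when part of it reflects who was diagnosed.

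**Working it through.** **1. The plan's own sample size.** Inputs: 5% versus 10%, two-sided 5%, 90% power. The log-odds-ratio formula is n = (1.960 + 1.282)² × [1/(0.05×0.95) + 1/(0.10×0.90)] / [ln OR]². The squared term is 10.507, the variance term 32.164 and ln OR = ln(2.111) = 0.7472. So n = 10.507 × 32.164 / 0.5583 = 605.3, rounded up to 606, and 606/0.85 = 712.9, rounded up to 713. Both stated figures are reproduced. The sample size is not in question.

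**2. Who enters the diagnosed-only model.** Intervention: 0.10 × 606 = 60.6. Control: 0.05 × 606 = 30.3, or 0.025 × 606 = 15.2 if the annual rate is halved for 6 months (an assumption). If screening finds everyone usual care would find, 60.6 − 30.3 = 30.3 intervention cases, half of them, have no control counterpart.

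**3. A worked example, 713 per arm.** Assumptions: intervention diagnosis uniform over 0.3 to 1 month, control diagnosis uniform over 6 months, exponential waits to treatment with means of 8 and 2 months.

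- Intervention, diagnosis at the midpoint of 0.65 months: share treated = 1 − exp(−5.35/8) = 0.488; 71.3 × 0.488 = 34.8 treated.
- Control: share treated = 1 − (2/6)(1 − exp(−3)) = 0.683; 35.65 × 0.683 = 24.4 treated.

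Of all randomised, 4.9% versus 3.4% are treated by 6 months, in favour of the intervention. Of the diagnosed, 49% versus 68% are treated, in favour of control.

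**4. Hazard ratios under the same set-up** (simulated trials, unadjusted Cox, median HR; repeat runs agreed within about 10%):

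| Mean wait, intervention vs control | Control rate | HR, all randomised | HR, diagnosed only |
|---|---|---|---|
| 5 vs 5 months | 5% | 3.34 | 2.12 |
| 5 vs 2 months | 5% | 2.00 | 1.11 |
| 8 vs 2 months | 5% | 1.48 | 0.65 |
| 5 vs 5 months | 2.5% | 6.63 | 2.20 |
| 5 vs 2 months | 2.5% | 3.99 | 1.09 |
| 8 vs 2 months | 2.5% | 2.97 | 0.67 |

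**5. Separating selection from real delay.** In step 4 the waits differ by arm, so part of the change could be a true delay. A second simulation (606 per arm, 26 weeks) splits people into those found in either arm and those found only by screening. Nobody in the first group is ever diagnosed or treated later under the intervention. The 17-week wait is anchored on the wait of over 4 months that the Introduction gives for one hospital trust. The other waits and the uptake are assumptions.

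| Control rate | Mean wait: either arm / screen-only (uptake in screen-only) | Treated, intervention / control | HR, all randomised | HR, diagnosed only | HR, those found in either arm |
|---|---|---|---|---|---|
| 5% | 17 / 17 weeks (100%) | 45 / 15 | 3.23 | 2.16 | 2.20 |
| 5% | 8 / 26 weeks (50%) | 37 / 21 | 1.80 | 1.00 | 2.96 |
| 5% | 4 / 26 weeks (50%) | 38 / 26 | 1.50 | 0.84 | 4.98 |
| 2.5% | 4 / 26 weeks (50%) | 29 / 13 | 2.31 | 0.49 | 4.90 |

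In the last two rows no one is slowed, more people are treated, and the diagnosed-only hazard ratio is still below 1. That is selection alone.

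**6. Time to testing and time to diagnosis.** The text does not name their population. If the diagnosed set were used, everyone in it would have the diagnosis event, so the model could not reflect extra detection.

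**The case against.** **Scope.** The restriction is explicit for time to treatment only, and the text calls it a secondary analysis. A reader might infer that all the time-to-event outcomes are compared only among the diagnosed. The document does not support that. Secondary outcomes and Follow-up describe which dates are extracted, and a time to diagnosis exists only for someone diagnosed, so extraction is compatible with a Cox model that censors everyone else. This stands. What remains is that the population for those two outcomes needs stating.

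**Detection is already measured.** The primary outcome captures it in all randomised participants, and an all-randomised hazard ratio for treatment mixes detection with speed. That is true. But the diagnosed-only ratio is not a clean measure of speed either: in step 5 it is 1.00 where the ratio among those found in either arm is 2.96. It recovers that ratio only when screen-only cases have the same waits and uptake as the rest (2.16 against 2.20).

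**Reversal rests on assumed waits.** This stands. The document does not give waits or uptake for screen-detected cases, and with equal waits the direction holds.

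**The economic model.** A reader might infer that it would be biased. That is not shown: the Health economic evaluation section takes times as inputs, not a hazard ratio, and models case identification as its own stage.

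**Summary measure.** Non-proportional hazards and the choice of cumulative incidence or restricted mean time belong to the analysis plan and are not pressed here.

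**Conclusion.** The point holds for time to starting treatment. Population, model and censoring are stated, and the population depends on the primary outcome, so the between-arm hazard ratio is not protected by randomisation. No all-randomised analysis of this outcome is described. For time to testing and time to diagnosis the point is conditional: a diagnosed-only analysis would have the same fault.

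The protocol's own rates fix the imbalance at about 61 versus 30 participants. The effect on the hazard ratio depends on assumptions: it is reduced from about 3.3 to 2.1 with equal waits, and falls below 1 under some unequal waits or lower uptake in screen-detected cases. A reader might infer that the sign will reverse. The calculations show only that it can. The primary analysis and the sample size are unaffected.

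**What to change.** - **Time to treatment.** In Statistical methods, make the between-arm analysis of time from randomisation to starting treatment include all randomised participants, with those who do not start censored at 6 months or last contact.
- **Time to diagnosis.** State the same population. State the population for time to testing too.
- **Diagnosed participants.** Report their intervals descriptively by arm, without a between-arm test or causal reading.
- **Interpretation.** Say that the all-randomised hazard ratio combines detection with speed.

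The cost is more than wording, because Follow-up excludes notes review for intervention test-negatives. The plan can assume that they start no OSA treatment within 6 months and check this against the 6-month questionnaire, which already asks about procedures to diagnose or treat moderate-to-severe OSA. That check covers only those who return it. Otherwise the notes check must be extended to them, which changes the protocol's stated position on access to records. Follow-up does not clearly cover intervention participants who never completed the test, so the chosen rule should name them as well.

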## Health economic evaluation

A trial-based economic analysis will be undertaken to assess the cost-effectiveness of the
use of AcuPebble in general practice compared with GP referral to hospital for the diagnosis
of people with moderate-to-severe OSA. Information about resource use will be collected
using resource use questionnaires and notes review, which will include equipment (AcuPebble
and home sleep RP) required, staff required and healthcare resource while participants are
awaiting referral and treatment. Resource use will be valued using national sources.^41^

Additionally, we will conduct a systematic literature review to identify existing economic
evidence regarding OSA diagnosis and in individuals with evidence of EDS/OSAS and treatment.
Insights from this and input from clinical experts will inform the model structure. In the
model, we will include a ‘no screening’ strategy to model the natural history
of people living with OSA, in addition to the two screening approaches: using AcuPebble in
general practice and GP referral to hospital-based standard care (home sleep RP). We
envisage the economic model will comprise two stages. In the first stage, we will use a
decision tree illustrative structure to model the short-term costs and benefits associated
with identifying people living with OSA and in individuals with evidence of EDS/OSAS
following screening. In the second stage, we will use a state transition Markov structure to
model the progression of events associated with moderate-to-severe OSA (eg, stroke, CVD,
myocardial infarction), and RTAs in those with individuals with evidence of EDS/OSAS, then
the long-term costs and benefits associated with treatment following the screening/no
screening strategies.

The economic model will require clinical and cost inputs related to the strategies.
Clinical inputs (eg, time to test, time to diagnosis and time to treat) will be obtained
from the clinical trial and supplemented with information from the literature (eg, rate of
moderate-to-severe people with OSA experiencing a stroke, associated costs and utility
values). The cost associated with using AcuPebble will be obtained from Acurable and costs
for GP referral to hospital-based standard care will encompass all resource use and costs
for GP referral using the home sleep RP. Resource use questionnaire will be developed using
the CSRI to capture healthcare associated with diagnosis and patient management while
awaiting referral and treatment (eg, healthcare professional visits, inpatient/outpatient
visits and medication) with information collected at baseline and 6 months. Resource
use will be valued using unit costs from national sources. Where costs are not available,
these will be obtained from published literature and adjusted using appropriate indexes. All
costs included will be those directly related to the UK NHS and personal social
services.

Outcomes in the form of QALYs will be calculated using data collected from the EQ-5D-5L.
The health-related quality of life information collected will enable us to estimate the
short-term impact of being screened on the participants’ quality of life. The EQ-5D
is a widely used generic measure of health-related quality of life that enables the
calculation of QALYs and is recommended for use in economic evaluations in healthcare.^42^ The EQ-5D-5L will comprise the descriptive
section and the accompanying VAS, which ask participants about their quality of life on a
specific day.

In line with NICE recommendations,^42^
costs incurred and benefits accrued will be discounted at 3.5% per annum, and the findings
will be presented as an incremental cost-effectiveness ratio in terms of costs per
additional life-year and QALY associated with each of the screening options over a lifetime
horizon. Additionally, we will present results to show the short-term (eg, additional cases
of moderate-to-severe OSA and in individuals with evidence of EDS/OSAS detected following
each screening strategy) and the long-term benefits of screening and treatment (eg,
reduction in strokes, CVDs and myocardial infarction). Several sensitivity and scenario
analyses will be undertaken to estimate the impact to the base case cost-effectiveness
results. The model will form the basis for conducting value of information analysis, which
will quantify the total expected cost due to the remaining uncertainty around the
cost-effectiveness of introducing screening for OSA/OSAS.

## Oversight, monitoring and quality assurance

The trial will be conducted in accordance with the current approved protocol, GCP, relevant
regulations, the Sponsor and Oxford PC-CTU’s SOPs and study-specific working
instructions. All principal investigators, coordinating centre staff and site staff will
receive training in trial procedures according to GCP where required. Regular monitoring
will be performed according to GCP using a risk-based approach. Data will be evaluated for
compliance with the protocol and accuracy in relation to source documents where
possible.

The composition, roles and responsibilities of various management committees are detailed
in their respective charters. These include the *Trial Management Group*
(*TMG*) which will be responsible for the monitoring of all aspects of the
trial’s conduct and progress and will ensure that the protocol is adhered to, and
that appropriate action is taken to safeguard participants and the quality of the trial
itself, and the *Research Steering Group* (*RSG*) which will
provide oversight of the research and will operate as the key forum through which the funder
shall be informed as regards progress and outcomes. An independent *Trial Steering
Committee* (*TSC*) will provide an overall supervision of the trial
and ensure it is being conducted in accordance with the principles of GCP. An independent
*Data Monitoring and Ethics Committee *will review and monitor the accruing
data to ensure the rights, safety and well-being of the trial participants. An
*Innovation and Implementation Monitoring Team* will be established to
assist Acurable in the development and commercialisation of the product to this new
market—GPs/primary care.

## Patient and public involvement

The study has collaboratively involved patients in the design and delivery of the research.
The research proposal was developed with input from the founder of Hope2Sleep and the
managing secretary of the Sleep Apnoea Trust Association. Once the study was funded, a third
patient was recruited to form a patient and public involvement (PPI) panel. The role of the
PPI panel is to work with the PPI lead to ensure that the patient perspective is taken into
consideration throughout the study. For example, the PPI group contributed to the
development of the study protocol and study documentation and are actively involved in the
study management committees (TMG, TSC, Research Steering Committee). They will be
instrumental in the interpretation of study findings and ensuring that the findings reach a
wide range of people.

All involvement activities will align with the UK Standards for Public Involvement, and
training and support will be provided where necessary. The public contributors will be
offered honoraria and expenses in line with recommendations from the National Institute for
Health and Care Research (NIHR) Centre for Engagement and Dissemination. The PPI lead will
be responsible for capturing the impact of involvement throughout the project and reporting
activities using the Guidance for Reporting Involvement of Patients and the Public
framework.^43^

## Ethics and dissemination

### Sponsor and governance arrangements

The University of Warwick will act as trial sponsor (SOC.09/22-23;
[contact]), which will be conducted by the Oxford PC-CTU. The trial will
be conducted in accordance with the Sponsor and PC-CTU’s SOPs. The study sponsor
and funders have no influence or authority over the study design, data collection,
analysis, reporting, etc.

###  Ethical approvals and reporting

The investigators will ensure that this trial is conducted in accordance with the
principles of the Declaration of Helsinki and with GCP.

Ethical approval was granted from the South Central Oxford A Research Ethics Committee on
9 June 2023 (23/SC/0188) (protocol amendment version 1.3; update with amendment and
approval to renumber to V2.0 on 29 August 2023).

The chief investigator will submit and, where necessary, obtain approval from the above
parties for all substantial amendments to the original approved documents. All approved
protocol amendments will be conveyed to the Trial investigators and, where appropriate,
participants.

The CI (or delegate) shall submit throughout the clinical trial, or on request, progress
report to the Research Ethics Commitee (REC) (where required), the Health Research
Authority (where required), the funder (where required) and the Sponsor (where required).
In addition, an end of trial notification and final report will be submitted to the REC
and the Sponsor.

## Trial registration

Prior to the recruitment of the first participant, the trial was registered on the ISRCTN
Database (16982033). Results will be uploaded to this register within 12 months of the end
of the trial date.

### Trial start and end dates

The trial started on 1 November 2022. Patient recruitment began on 7 January 2024.
Initial planned end date will be on 31 April 2025.

### Notification of serious breaches to GCP and/or trial protocol

The management of non-compliances will be informed by the Oxford PC-CTU’s
SOPs.

### Trial protocol deviation and violations

A trial-related deviation is a departure from the ethically approved trial protocol or
other trial document or process (eg, consent process or administration of trial
intervention) or from GCP or any applicable regulatory requirements. Any deviations from
the protocol will be documented in a protocol deviation form and filed in the trial master
file.

A PC-CTU’s SOP is in place describing the procedure for identifying
non-compliances, escalation to the central team and assessment of whether a
non-compliance/deviation may be a potential serious breach.

